### Statistical analysis

#### Sample size

Sample size was calculated separately for each cohort according to its main disease-specific primary outcome, as well as with 24-months changes in LLFDI score as global primary outcome. The estimated sample size aiming for a sample that allowed the disease-specific objectives as well as the global objectives to be met.

*Cohort specific sample size calculations*. Sample size calculation for each disease cohort showed that 600 participants will be required in each cohort in order to achieve a statistically significant outcome of the respective hypothesis critical value with a power of 90% and an alpha error of 0.05. Details of the hypotheses and the assumption underpinning these calculations are summarised in Table 2.

*Global sample size calculations*. Sample size calculation for the global primary outcome is based on the hypothesis that baseline real-world walking speed is associated with changes in LLFDI score (0–100) within 24 months. Using (i) a minimal detectable change of 95% confidence of 3.41 in LLFDI functional component [53] representing a clinically relevant intervention effect [54], (ii) a standard deviation of the mean change in LLFDI functional component of 30.1 points [41], (iii) a standard deviation of 0.29 m/s for real-world walking speed [55], (iv) a clinically relevant and measurable difference of 0.1 m/s in real-world walking speed between two patients [56], and (v) based on a linear regression analysis a sample size of 67 subjects would allow identifying a statistically significant change, with a power of 80% and an alpha error of 0.05. Including an expected drop-out rate of 10–30% the final sample size would be n = 81. The available sample size of 2,400 patients, derived from the sum of sample sizes required for the evaluation of the abovementioned cohort-specific outcomes provides sufficient power to test the general LLFDI hypothesis.

The proposed statistical method will be amended upon data completion and prior analysis should the data distribution require a more appropriate methodology.

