#### Clinically relevant outcome measures (constructs)

A wide range of core and cohort specific outcome measures will be collected, spanning patient-reported outcomes (PRO), observer-reported outcomes (ObsRO), clinician-reported outcomes (ClinRO), performance-based outcome physical measures (PerfO-P), and performance-based outcome cognitive/mental measures (PerfO-C). The assessments will be completed according to the assessment schedule (Fig 1), with all outcome measures detailed in Table 2.

**Table 2 pone.0269615.t002:** Cohort specific sample size calculation.

Cohort	Hypothesis	Critical value	Time frame	Assumptions	Loss to follow-up	Statistical method proposed	Sample size
Parkinson’s Disease	Reduced gait speed is associated with increased fall risk	a coefficient of 1 for a 1 m/s decline in walking speed	24 months [57]	(i) a standard deviation of real‐world walking speed of 0.11 m/s or higher [58, 59], (ii) a 2‐y rate of falls of 1.6 or higher [59]	20%	Poisson regression model	600
Multiple Sclerosis	Reduced RWS is associated with fall frequency	a coefficient of >0.5 for a 1 m/s decline in walking speed	24 months	(i) a standard deviation of real‐world walking speed of 0.13 m/s or higher (19), (ii) a 2‐y rate of falls of 5 or higher [60, 61]	10%	Poisson regression model	600
Chronic Obstructive Pulmonary Disease	RWS is associated with COPD exacerbations	an odds ratio of 1.43 for a 0.1 m/s decline in walking speed [62]	12 months	(i) a standard deviation of real‐world walking speed of 0.115 or higher [55]l, (ii) a proportion of exacerbations up to 0.6 [24, 62, 63]	30% [24, 62, 63]	Logistic regression model	600
Proximal Femoral Fracture	RWS is associated with care home admission	odds ratio of 2.55 in the risk of admission on slow RWS vs normal/high RWS [64]	6 months	(i) a ratio of low RWS vs normal/high RWS of 1:2, (ii) a six month proportion of admissions to care home of 10 to 30% [46, 65]	30% [46, 65]	Logistic regression model	572 (≈600)

RWS, real world walking speed.

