#### Analysis plan

The statistical analysis will follow a pre-specified step-wise procedure. We will elaborate a Statistical Analysis Plan including the definition of analysis sets, details on data edition (including derivation of new variables), handling of missing data and statistical analysis (including prioritisation of outcomes).

Descriptive analysis of main characteristics of patients, including detailed description of COAs and DMOs, will be done by number and percentage for categorical variables, mean and standard deviation for continuous variables with normal distribution, and median and percentiles 25th-75th for continuous variables with non-normal distribution.

We will test construct validity (convergent and known-groups). For convergent validity, we will test the correlation (Pearson or Spearman, depending on variables distribution) between DMOs and related constructs. A table of expected correlations for each DMO-construct combination will be built based on existing literature. For known-group validity, we will use one-way ANOVA test and pairwise comparisons of means between groups a priori expected to have differences in DMOs values. To test predictive capacity of DMOs against the disease-specific and global outcomes we will estimate the association between baseline DMO levels and each outcome using multivariable regression models (specific models depending on outcome distribution) adjusting for confounders. Non-linear associations will be tested using generalised additive models and appropriate transformation of variables will be done consequently. Secondary analyses will include use of DMO changes over time as predictors, and adjusting for baseline levels as sensitivity analysis. The ability of each DMOs to predict disease-specific and global outcomes will be compared to that of traditional predictors and predictive scores.

To quantify the ability to detect change of DMOs, we will calculate the change (between baseline and different follow-up periods) and the standardised response mean (SRM) in (1) groups defined by the self-reported change in mobility, (2) groups defined according to having had a clinically relevant event (e.g., an exacerbation in COPD, a fall in Parkinson) during follow-up, and (3) groups defined according to clinically relevant changes in anchors.

We will establish the MID by triangulation using anchor- and distribution-based estimates.

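### Table 2's Parkinson's inputs need about 679 enrolled for 90% power, not 600; 600 gives about 86% if dropouts contribute nothing and about 88–90% if part of their follow-up counts

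*Protocol article*

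**What the plan says.** The Sample size section says of the cohort calculations: "Sample size calculation for each disease cohort showed that 600 participants will be required in each cohort", to detect each row's critical value "with a power of 90% and an alpha error of 0.05". It does not say whether alpha is one- or two-sided. The assumptions are in Table 2.

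- **PD row:** Poisson regression for falls over 24 months; effect "a coefficient of 1 for a 1 m/s decline in walking speed"; an SD of real-world "walking speed of 0.11 m/s or higher"; a two-year "rate of falls of 1.6 or higher"; 20% loss to follow-up; sample size 600.
- **COPD row:** logistic regression for exacerbations over 12 months; odds ratio 1.43 per 0.1 m/s; SD 0.115 or higher; an event proportion given only as an upper bound of 0.6; 30% loss; sample size 600.

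Three other statements bear on the point. The study flow section keeps the data of participants who drop out up to withdrawal, unless they withdraw consent. The Diaries section has PD participants return falls diaries monthly. For predictive capacity, the Analysis plan says "we will estimate the association between baseline DMO levels and each outcome using multivariable regression models", with adjustment for confounders.

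**The concern.** The text presents 600 as the result of each cohort's calculation. The PD row gives every input needed to repeat that calculation, and the answer is larger than 600. Table 2 shows rounding openly in the hip-fracture row, where 572 is marked as approximately 600 and is rounded up. The PD row carries no such mark, and going from 679 to 600 would be rounding down by 79 participants.

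Fall frequency is the PD cohort's specific primary outcome, and the study is meant to support regulatory acceptance of digital mobility outcomes. A null PD result would be read against a 90% power claim that the table's inputs, taken at face value, do not support.

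**Working it through.** **PD inputs (Table 2 and Sample size):** coefficient b = 1 per 1 m/s; SD = 0.11 m/s; rate = 1.6 per two years; loss 20%; power 90%; alpha 0.05, taken as two-sided.

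*Attempt to reproduce 600.* For Poisson regression on a normal covariate:

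n = (z₀.₉₇₅ + z₀.₉₀)² / (rate × SD² × b²)

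- Numerator: (1.960 + 1.2816)² = 10.507
- Denominator: 1.6 × 0.11² × 1² = 0.01936
- n = 10.507 / 0.01936 = 542.7, so 543 evaluable
- Enrolled at 20% loss: 543 / 0.8 = 679

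Alternatives tried:

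| Variant | Enrolled |
|---|---|
| Two-sided, 90%, n/(1 − 0.2) | 679 |
| Two-sided, 90%, n × 1.2 | 652 |
| Two-sided, 80%, n/(1 − 0.2) | 508 |
| One-sided, 90%, n/(1 − 0.2) | 554 |
| Two-sided, 90%, **10%** loss, n/(1 − 0.1) | 604 |
| Two-sided, 90%, **10%** loss, n × 1.1 | 598 |

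The Signorini form gives 541.4 evaluable, so the choice of formula is not the explanation. Only a 10% loss comes close to 600, and the row states 20%.

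*PD power with 600 enrolled.* Power = Φ(√(n × 0.01936) − 1.960). Let f be the fraction of follow-up that a dropout contributes. The full-follow-up equivalent is n = 600 × (0.8 + 0.2f).

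| f | n | Power |
|---|---|---|
| 0 (complete loss) | 480 | Φ(3.048 − 1.960) = 86.2% |
| 0.25 | 510 | Φ(3.142 − 1.960) = 88.1% |
| 0.50 | 540 | Φ(3.233 − 1.960) = 89.9% |
| 0.75 | 570 | Φ(3.322 − 1.960) = 91.3% |

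Simulated Poisson regressions gave 86.0% at 480 (2,000 runs). With an exposure offset and dropouts leaving evenly over 24 months, they gave 89.3% (3,000 runs). The values of f are assumptions; the article gives no dropout timing.

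*What would restore 90% with 480 evaluable:* a rate of 10.507 / (480 × 0.0121) = 1.81, or an SD of √(10.507 / (480 × 1.6)) = 0.117 m/s.

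**COPD inputs (Table 2):** log odds ratio per SD, B = ln(1.43) × 1.15 = 0.411, so B² = 0.169; loss 30%, so 600 enrolled leaves 420 evaluable.

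n = 10.507 / (p(1 − p) × B²); power = Φ(√(420 × p(1 − p)) × B − 1.960)

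| p | Evaluable | Enrolled (÷ 0.7) | Power at 420 |
|---|---|---|---|
| 0.6 | 259 | 370 | 98.5% |
| 0.5 | 248 | 355 | 98.8% |
| 0.4 | 259 | 370 | 98.5% |
| 0.2 | 388 | 555 | 92.1% |
| 0.18 | 421 | 601 | 89.9% |
| 0.15 | 487 | 696 | 85.3% |

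The requirement depends on p(1 − p), so it is the same at 0.6 and 0.4 and rises only as p moves further from 0.5.

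**Cross-check on the other rows.** For MS (coefficient 0.5, SD 0.13, rate 5, 10% loss), 10.507 / (0.25 × 0.0169 × 5) = 497.4, so 498 / 0.9 = 554 enrolled. There 600 suffices, with about 92% power at 540 evaluable. The hip-fracture 572 is matched at about 15% admissions (399 / 0.7 = 570), inside the stated 10 to 30%.

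**The case against.** The strongest reply is that 20% loss need not remove 20% of the information. The article keeps data up to withdrawal and collects PD falls monthly, and in a Poisson model information scales with person-time. If those lost leave evenly over 24 months, 600 enrolled are worth 540 full-follow-up equivalents against 543 needed, and power is 89.9%. This stands as far as it goes, and it is why a flat 86% is not established. But the article states no person-time allowance, the 89.9% needs an assumed dropout pattern, and with a quarter of follow-up the figure is 88.1%.

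Sidedness is unstated. One-sided alpha would need 554, and 600 would then give 92.0% even with complete loss. Two-sided is the usual reading, and one-sided does not reproduce 600 either.

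The SD and rate are floors, so true power may be higher. That is fair, but the floors define the case for which the sample-size claim has to hold.

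Two stronger readings are tempting and not supported:

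- **PD power far below 86% after confounder adjustment.** Adjustment would lower power, because Table 2 makes no allowance for it. The article gives no figure for the walking-speed variance that confounders explain, so the size of the drop cannot be derived.
- **COPD underpowered.** At the only stated proportion 600 is more than enough. A lower proportion does not need more patients between 0.6 and 0.4. Values such as 0.18 or 0.15 are not in the article.

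**Conclusion.** The PD row does not support the statement that its calculation showed 600. At its own floor values, with two-sided alpha and the usual inflation for loss, it needs 543 evaluable and about 679 enrolled. With 600 enrolled, power is about 86% if dropouts contribute nothing, and about 88–90% if their data are used with an exposure offset and cover a quarter to a half of follow-up. The supported shortfall, before covariate adjustment, therefore runs from about 4 points to almost none, depending on dropout timing that the article does not give. Why 600 agrees with a 10% loss cannot be told from the document.

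The COPD row is a secondary reporting point: its 600 is not reproduced at 0.6, and an upper bound alone does not secure 90% power, which is lost once the proportion is under about 0.18. No COPD shortfall is shown.

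Severity is minor to moderate: the power claim concerns a cohort-specific primary outcome, but no test or estimand changes.

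**What to change.** 1. In the PD row, do one of three things, according to what was actually done: state 600 enrolled with about 86% power under complete loss of dropouts (and that 90% needs about 679); correct the loss figure if 10% was used; or state the person-time allowance and the power it gives.
2. State that alpha is two-sided.
3. In the COPD row, add the range of proportions for which 420 evaluable participants give 90% power: about 0.18 or higher, up to 0.6. Mark it as a derived figure, not as an assumption that the authors made.
4. Replace the claim that each calculation showed 600 to be required with a statement that a common size of 600 was chosen, and give the power for each cohort.

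The cost is a few sentences and two table rows. No additional participants are needed; the stated PD power may become slightly less favourable.

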The MS population will be based on the revised McDonald’s criteria, with mild to moderate disability., Patients will be recruited covering a wide spectrum of overall disability and varying severity of walking impairment, with Expanded Disability Status Scale from 3—fully ambulatory but with mild to moderate disability in other functional systems—to 6.5 –indicating reduced walking distance and requiring walking aids to walk 20 meters without resting. They will also have had disability progression over the previous two years, to enrich the sample with patients who are likely to progress over the next two years. Patients with a recent relapse (30 days before screening) will be excluded in order to have a reliable mobility measure not impacted by the recovery from a relapse.

The PFF cohort will be recruited either during the acute postoperative or subacute phase (max. 52 weeks) following sustaining a hip fracture. All PFF participants are community dwelling at point of enrolment; care home residents will not be included due to their increased burden of comorbidities likely to bias mobility results. Enrolling acute PFF patients allows monitoring of mobility during the recovery phase over the first 12 months providing unprecedented analysis of mobility trajectories over a long period of time in a disease cohort where mobility impairment is the direct consequence of a major trauma. Enrolling subacute PFF participants will allow a longer follow-up of mobility to focus on functional decline in a population with a high prevalence of frailty and sarcopenia. The aim is to study a mixed population of older community-dwelling adults to capture those who received for informal and formal care as well as participants who were independent prior to sustaining a hip fracture.

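### Table 2 shows no allowance for the planned confounder adjustment, so the stated 90% power is not shown to hold for the adjusted models

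*Protocol article*

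**What the plan says.** Under Sample size, the protocol article states that "600 participants will be required in each cohort" to detect the respective "hypothesis critical value with a power of 90% and an alpha error of 0.05". It adds: "Details of the hypotheses and the assumption underpinning these calculations are summarised in Table 2".

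Table 2 names a Poisson model for falls in PD and MS, and a logistic model for exacerbations in COPD and for care home admission after proximal femoral fracture (PFF). Each row gives an effect, the spread of walking speed (in PFF a 1:2 split of slow to normal/high), an event rate or proportion, and a loss to follow-up. The PD effect is "a coefficient of 1 for a 1 m/s decline in walking speed" and the MS effect is "a coefficient of >0.5 for a 1 m/s decline in walking speed". No row mentions covariates, an R² or a variance inflation factor.

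Under Analysis plan, predictive capacity against the disease-specific and global outcomes is to be estimated "using multivariable regression models (specific models depending on outcome distribution) adjusting for confounders". No confounders are named.

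**The concern.** The sample size paragraph and the Analysis plan concern the same associations: baseline walking speed with each cohort's primary outcome. The listed assumptions are those of a model with walking speed alone, while the planned test is adjusted. If walking speed is correlated with the confounders, only its residual variance informs the adjusted coefficient, and the required sample grows by 1/(1 − R²).

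Some correlation is plausible. The Introduction says walking is affected by age-associated processes and chronic disease, and the eligible age ranges are wide. An R² of 0.1 needs a multiple correlation of only 0.32 (√0.1).

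At stake is how a null adjusted result would be read. In a study that seeks regulatory acceptance, it could be taken as evidence from a 90%-powered test when the planned model may have had less.

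**Working it through.** **Inputs (Table 2).**
- PD: coefficient 1 per m/s, SD 0.11 m/s, 1.6 falls over 2 years, 20% loss.
- MS: coefficient 0.5 per m/s, SD 0.13 m/s, 5 falls over 2 years, 10% loss.
- COPD: odds ratio 1.43 per 0.1 m/s, SD 0.115 m/s, proportion with exacerbation up to 0.6, 30% loss.
- PFF: odds ratio 2.55, split 1:2, 10 to 30% admitted, 30% loss.

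Alpha is 0.05, taken as two-sided because the article does not say. Evaluable numbers from 600 are PD 600 × 0.8 = 480, MS 600 × 0.9 = 540, and COPD and PFF 600 × 0.7 = 420. **R² is an assumption**, shown from 0 to 0.3.

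**The plan's own figures, without covariates.** For Poisson regression, n = (1.960 + 1.282)² / (rate × coefficient² × SD²), with numerator 10.507.
- MS: 10.507 / (5 × 0.25 × 0.0169) = 10.507 / 0.021125 ≈ 498 evaluable, or 553 enrolled. Not 600.
- PD: 10.507 / (1.6 × 1 × 0.0121) = 10.507 / 0.01936 ≈ 543 evaluable, or 679 enrolled. Not 600. One-sided alpha gives 553.
- PFF: 572 is closely matched without covariates: 570 by a two-proportion formula at 15% admitted overall, or 584 by a Wald calculation with 10% admitted in the normal/high group.

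**Power of the adjusted Poisson models.** Power = Φ(√(n × rate × coefficient² × SD² × (1 − R²)) − 1.96). For MS at R² = 0.2: √(540 × 0.021125 × 0.8) = 3.021, and Φ(1.061) = 85.6%.

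**PFF.** The log odds ratio is ln 2.55, with variance [3/(p₁(1 − p₁)) + 1.5/(p₀(1 − p₀))] / (420 × (1 − R²)). Here p₁ and p₀ are the admission proportions in the slow and normal/high groups that give the stated overall proportion. At 15% overall, p₀ = 0.107 and p₁ = 0.235.

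| Cohort (evaluable) | R² 0 | 0.1 | 0.2 | 0.3 |
|---|---|---|---|---|
| MS (540) | 92.2% | 89.3% | 85.6% | 80.7% |
| PD (480) | 86.2% | 82.4% | 77.8% | 72.3% |
| PFF, 10% admitted (420) | 81.3% | 77.1% | 72.1% | 66.4% |
| PFF, 15% admitted (420) | 92.1% | 89.3% | 85.5% | 80.6% |
| PFF, 20% admitted (420) | 96.4% | 94.6% | 91.9% | 88.2% |
| PFF, 30% admitted (420) | 98.8% | 98.0% | 96.6% | 94.2% |

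Simulated adjusted Poisson models (2,000 runs per setting) gave 93.1, 88.9, 84.6 and 79.4% for MS and 86.1, 83.1, 78.7 and 74.0% for PD, within about 2 points of the formula.

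**Room for adjustment at 90% power.**
- MS: 1 − 497.4/540 = 0.08.
- PD: none.
- COPD at 60% events: the log odds ratio per SD is ln(1.43) × 1.15 = 0.411, so n = 10.507 / (0.24 × 0.411²) ≈ 259, and the room is 1 − 259/420 = 0.38.

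**The case against.** Four points weigh against the concern.

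1. The article never says that the 90% is for a model with walking speed alone. A reader might infer this from Table 2, but the figures do not establish it. Only the PFF number is matched without covariates. The MS 600 exceeds the unadjusted 553 and is nearer to the 615 needed at R² = 0.1 (553/0.9), so an unlisted allowance cannot be excluded. The article also does not say whether its effect sizes are crude or adjusted. This stands, and it limits the point to what is shown.

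2. R² is unknown and the confounders are unnamed. It is tempting to argue that R² must be large in MS because, as Cohort descriptions says, "Patients will be recruited covering a wide spectrum of overall disability and varying severity of walking impairment". But the article lists the EDSS, its disability scale, as a secondary outcome measure used as a construct, not as a confounder. The size of the loss is therefore conditional. This stands.

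3. The MS and PD inputs are lower bounds, as in PD's "walking speed of 0.11 m/s or higher". In MS with 540 evaluable, an SD of 0.14 gives 90.2% at R² = 0.2, and a rate of 6 gives 91.1%. This stands as a caveat. The 90% is nonetheless claimed on the stated values.

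4. A journal article condenses, and covariate choice belongs in the analysis plan. That excuses the missing list of confounders. It does not settle the mismatch here, because the article gives a power figure, says where its assumptions are summarised, and itself fixes an adjusted analysis.

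**Conclusion.** The stated 90% is not shown to hold for the planned adjusted models. The stronger statement, that it fails, would need an R² that the article does not give.

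At Table 2's floor inputs, with two-sided alpha and the stated losses:
- **MS** keeps 90% only up to R² of about 0.08, and has 81 to 89% over R² of 0.3 to 0.1.
- **PD** is at about 86% before any adjustment, so part of its shortfall is a separate mismatch with its own inputs. Adjustment lowers it to 72 to 82%.
- **PFF** depends on the admission proportion. At 10% overall it is short without adjustment, near 15% adjustment decides the matter, and at 20% or more it tolerates R² of at least 0.2.
- **COPD** at 60% events keeps 90% up to R² of about 0.38.

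These figures assume the plan's Poisson and logistic models and the (1 − R²) approximation. Larger true SDs or fall rates would offset part of the loss in MS and PD. The planned enrolment is not called into question.

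**What to change.** Keep 600 per cohort. In the Sample size section and Table 2:
- say which model the 90% refers to, and whether alpha is two-sided;
- reconcile the PD figure with its own inputs, which give about 86% unadjusted after 20% loss;
- report the power of the planned adjusted model in each cohort at R² of 0.1, 0.2 and 0.3, and for PFF across the stated admission range;
- note that the MS and PD inputs are lower bounds, so larger SDs or rates would recover part of the loss.

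Once the confounders are fixed, each cohort's R² can be estimated from baseline data without using outcomes. Trial status reports 1,800 participants recruited by March 2022.

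The cost is some wording and one line of calculation per cohort. The downside is a less favourable stated power in PD, probably in MS, and in PFF at low admission proportions.
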